### Statistical analysis

Baseline characteristics of the two intervention groups and control group with regard to the most important prognostic indicators and main outcome measures will be compared to assess the adequacy of the randomization. If necessary, adjustments will be made for baseline characteristics. In a similar way, we will assess differences between responders and non-responders with regard to the most important prognostic indicators in order to describe the generalizability of the results.

Data are analyzed according to the intention-to-treat principle. In addition, per protocol analysis will be performed, in which only patients will be included who attained 75% of all exercise sessions.

Scores on the self-report measures of fatigue, mood state and health-related quality of life will be calculated according to published scoring algorithms. Multilevel longitudinal regression analysis will be conducted to assess changes in each outcome measure. The follow-up measurements will be defined as dependent variable and the following levels are used, 1) time of follow-up measurement (values corresponding with performance at t1 and t2); 2) training centre 3) individual. Regression coefficients will indicate differences between interventions and control group. Regression models will be adjusted for gender, baseline values, and compliance. Missing values will be avoided as much as possible by asking participants to comply with the post-treatment and follow-up measurement even after they drop out from the exercise programme. In the event of missing values, the mixed linear regression modelling will account for them.

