### Recruitment and randomization

The patients are recruited from three hospitals in the southern part of the Netherlands: Máxima Medical Center (Veldhoven/Eindhoven), Catharina Hospital (Eindhoven), and Elkerliek Hospital (Helmond). Expectations are that more hospitals in the southern part of the Netherlands will be invited to collaborate.

In consultation with the treating medical oncologist, the oncology nurse determines if patients in their clinical setting are eligible for the study. All potentially eligible patients receive written information to take home. Next, patients are contacted by telephone and invited to query any question about the study. Patients who are willing to participate are asked to provide written informed consent.

After completing all baseline measurements, patients are stratified by tumour type and hospital and randomly assigned to one of the following groups: 1) high intensity exercise programme or 2) low-to-moderate intensity exercise programme. Next, patients from both groups are randomly assigned to immediate training or waiting list (i.e. waiting list control group). After 12 weeks, patients of the waiting list control group start with the exercise programme they have been allocated to. The research assistant uses statistical software for randomization of the sample and informs patients about the results. Allocation sequence is concealed from the medical team. Study outcomes are assessed by a blinded professional and patients are instructed not to reveal their treatment allocation.

Patients who choose not to participate in the REACT study are asked to complete a one time survey. This questionnaire includes relevant characteristics, the reason for not participating and questions on the current attitudes towards and beliefs about exercise.

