## Discussion

This project aims to contribute to evidence-based practice in cancer rehabilitation programmes. We evaluate the effectiveness of exercise in cancer patients with respect to improving physical fitness and reducing fatigue. Preliminary results in the literature are promising. Yet, the suggested positive physical and psychosocial outcomes of exercise programmes among cancer patients need to be confirmed in large, well-designed trials.

The REACT study evaluates the effectiveness and cost-effectiveness of a high intensity exercise programme compared to a low-to-moderate exercise programme, and a waiting list control group. In this way, we will obtain more insight in outcomes of different training intensities. Furthermore, if exercise appears effective, it becomes vital to evaluate cost-effectiveness and cost savings for health care utilization since exercise-based rehabilitation programmes do not yet form part of standard cancer care for cancer patients and survivors.

The following suggestions made by the systematic reviews have been incorporated to strengthen our methodology; applying a larger sample and long-term follow-up measurements, incorporating randomization of patients to appropriate comparison groups, including concealed allocation and blinded outcome assessment, and using intention-to-treat and per protocol analyses. Most studies so far have focused on breast cancer patients [16-18]. The inclusion criteria of the present study include as many as four cancer diagnoses (primary breast, colon or ovarian cancer, or lymphomas) allowing to explore whether patients with different cancer types respond differently to exercise. Furthermore, detailed evaluation of current attitudes towards and beliefs about exercise of both responders and non-responders are obtained. This provides insight concerning the generalizability of the results from this RCT.

Limitations of the study should be noted as well. Instead of a 'true' non-exercising control group, the present study includes a waiting list control group. Due to the growing availability of cancer rehabilitation groups in daily clinical practices in the study region, patients' expectations may not be met, and higher drop-out rates could occur with a non-exercising control group. However, the use of a waiting list control group does not allow long-term follow-up measurements, because after 12 weeks these patients start the exercise programme they have been allocated to.

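### Tumour type, a stratification factor, is missing from the stated model; hospital's place in it is unclear; and further adjustment is triggered by observed baseline imbalance

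*Protocol article*

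**What the plan says.** Recruitment and randomization: after baseline measurement, "patients are stratified by tumour type and hospital and randomly assigned to one of the following groups", namely high or low-to-moderate intensity. A second random step then assigns immediate training or waiting list. On sites, "The patients are recruited from three hospitals in the southern part of the Netherlands", and more hospitals are expected to be invited. Four tumour types are eligible.

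Statistical analysis: the multilevel model has follow-up time as its first level, followed by "2) training centre 3) individual". Its covariates are listed: "Regression models will be adjusted for gender, baseline values, and compliance". Neither tumour type nor hospital is named.

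The same section says that the three groups' baseline prognostic indicators and main outcome measures "will be compared to assess the adequacy of the randomization". The next sentence is "If necessary, adjustments will be made for baseline characteristics". No covariates and no criterion are attached to it.

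**The concern.** There are two linked problems.

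First, stratification forces the groups to be alike on tumour type and hospital, so part of the outcome variance can no longer contribute to chance differences between them. A model without those factors leaves that variance in the residual and reports a standard error larger than the true one. The benefit of stratifying is partly lost.

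Second, the article lets a look at the observed groups decide which covariates enter. If allocation was properly random, any imbalance is chance. The comparison therefore does not test the adequacy of randomisation, and the size of an imbalance does not show whether a variable predicts outcome. The trigger is also badly suited to tumour type. Stratification makes that factor balanced, so an imbalance rule would rarely select it, however prognostic it is. With no stated rule, the primary estimate can depend on a choice made after seeing data. The choice recurs for every primary measure: peakVO2, grip strength, chair stand, five MFI subscales and four FQL subscales.

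**Working it through.** **1. The plan's own figure.** Power calculations gives a fatigue difference of 9, SD 20, power 0.80 and two-sided alpha 0.05. Per group, n = 2 × (1.96 + 0.84)² × (20/9)² ≈ 78, which agrees with the stated 80. Power at 80 per group: the standard error is 20 × √(2/80) = 3.162, 9/3.162 = 2.846, and Φ(2.846 − 1.96) = 0.812. Read as 80 in total, power would be 0.52, so 80 is per group.

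**2. Cost of omitting the strata.** Let R² be the share of residual variance that tumour type and hospital explain beyond gender and baseline value. The documents give no R², so a range is shown. Assume that SD 20 is the residual SD of the stated model and that stratification achieves close balance. The true standard error is then 3.162 × √(1 − R²), while the model without the strata reports 3.162.

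- Actual alpha without strata = 2 × [1 − Φ(1.96/√(1 − R²))]
- Power without strata = Φ(2.846/√(1 − R²) − 1.96/√(1 − R²))
- Power with strata = Φ(2.846/√(1 − R²) − 1.96)

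| Assumed R² | Actual alpha, strata omitted | Power, omitted | Power, included | Loss (points) |
|---|---|---|---|---|
| 1% | 0.049 | 0.813 | 0.816 | 0.3 |
| 2% | 0.048 | 0.815 | 0.820 | 0.5 |
| 5% | 0.044 | 0.818 | 0.832 | 1.3 |
| 10% | 0.039 | 0.825 | 0.851 | 2.6 |
| 20% | 0.028 | 0.839 | 0.889 | 5.0 |

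Example at 10%: √0.90 = 0.949, 1.96/0.949 = 2.066 and 2.846/0.949 = 3.000. Power is Φ(3.000 − 2.066) = 0.825 without the strata and Φ(3.000 − 1.96) = 0.851 with them.

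**3. The conditional step.** A simulation under no treatment effect used 120 per arm, simple randomisation, five independent covariates and 8,000 runs. The Monte Carlo standard error is √(0.05 × 0.95/8000) ≈ 0.0024.

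| Approach | Type I error, 2% of variance per covariate | Type I error, 5% per covariate |
|---|---|---|
| One fixed model (none or all covariates) | 0.050 | 0.053–0.054 |
| Mechanical: adjust where the imbalance has p < 0.05 | 0.048 | 0.046 |
| Smallest p-value of no, full or triggered adjustment | 0.066 | 0.078 |

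The last row is the worst case for those three options. A rule followed mechanically does not inflate the error rate; an unconstrained choice can.

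**4. Cost of including the strata.** Tumour type takes 4 − 1 = 3 degrees of freedom and three hospitals take 3 − 1 = 2. That makes 5, out of 140 + 140 + 120 = 400 patients.

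**The case against.** The strongest reply has four parts.

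- **The article is a condensation.** The candidate covariates and the adjustment criterion may be in an analysis plan that is not shown, and tumour type may be among the prognostic indicators. This stands as far as missing detail goes. It does not cover what the article itself states: a covariate list without tumour type, and adjustment triggered by a baseline comparison.
- **Hospital may already be in the model.** Training centre is a level and may carry hospital wholly or in part. This stands: omission is certain for tumour type only.
- **The gain is small.** Gender and baseline value are fixed in advance and absorb part of the same variance. Gender overlaps with tumour type, since ovarian and most breast cancer patients are women. This also stands, and it favours the lower rows of assumed R².
- **Nothing announces free choice among models.** This is correct. The text fails to exclude it, which is a weaker fault than planning it.

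**Conclusion.** The point holds in a limited form and is worth correcting, but it does not threaten the trial's validity. Tumour type is stratified on and is missing from the stated model, hospital's relation to training centre is undefined, and further adjustment hangs on observed imbalance. For an assumed R² of 1–10%, omitting the strata costs about 0.3 to 2.6 points of power at 80 per group, with actual alpha about 0.049 to 0.039. These figures rest on the assumed R² and on stratification having produced close balance.

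Three stronger readings are tempting, and the documents do not support them.

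- A reader might infer that both stratification factors are left out. The training-centre level leaves that open for hospital.
- A reader might infer that the omission inflates the 5% error rate. It does the opposite. Inflation appears only under discretionary choice among models (0.066 to 0.078 in the worst-case simulation), which the article permits but does not plan.
- A reader might take R² of 5–15% and conclude that 280 × 0.05 = 14 to 280 × 0.15 = 42 patients' worth of information is lost in the comparison of the two exercise groups. That range is itself an assumption. It also overcounts, because with balance forced the estimate is already precise and only the reported standard error is too large. Matching power in the model above gives a loss of 3.5% to 10.5%, or about 10 to 29 of 280, and about 2 at an R² of 1%.

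**What to change.** In Statistical analysis:

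- Add tumour type and hospital as prespecified fixed effects in every primary model, or state that training centre is the hospital. Where the two differ, keep the training-centre level as well.
- Delete the sentence that makes adjustment conditional, and drop the claim that comparing the groups assesses the randomisation. Present baseline characteristics descriptively.
- Label any further covariate adjustment as a sensitivity analysis.
- Limit contrasts with the waiting-list group to t1. Those patients start training after 12 weeks, and the Discussion itself says that this group does not support long-term comparison.

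Whether compliance belongs in the model is a separate question, which this change does not settle.

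The cost is a change of wording and about 5 degrees of freedom out of 400 patients, slightly more if further hospitals join. Both factors are known at randomisation, so no new data are needed.

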### Study Outcomes

All studies within A-CaRe Clinical Research use similar methodologies and a comparable set of outcome measures [25]. Within the REACT study, primary and secondary outcome measures are assessed at baseline (t = 0) at the time of inclusion in the trial (4-6 weeks after ending chemotherapy), 12 weeks after randomization (t = 1), and 64 weeks after randomization (t = 2). For logistic reasons, all physical tests are conduced centrally at Máxima Medical Center in Eindhoven. All professionals follow detailed and standardized test protocols. The questionnaires can be completed at home or via internet.

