### Secondary outcome measures

The REACT study assesses the following secondary outcome measures: health-related quality of life, body composition, bone mineral density, neuropathy, objective and self-reported daily physical activity level, mood and sleep disturbances, functioning in daily life, return to work, cost from a social perspective, adverse events, compliance and satisfaction with the intervention. In addition, clinical data, disease status and treatment, sociodemographic characteristics, moderating variables of the exercise programme and adverse events will be recorded. A complete overview of primary and secondary outcome measures is provided in Table 1. A small selection of these secondary measures is described in detail below. A detailed description of the secondary outcome measures, common to all four trials, are described in an overall design paper [25].

**Table 1 T1:** Overview Primary and Secondary outcome measures

Outcome measures	Instrument

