**B. Secondary outcome measures**	

Sociodemographic data	Age, education, marital status, living situation, comorbidities and life style variables (e.g. smoking)

Clinical data	

Medical history	Date of diagnosis, subtype of disease, stage of disease, history of therapy

Disease status and treatment	Response to treatment, progression or relapse of disease and data on any additional treatment will be recorded from medical records

Adverse events	Medical records, reports of the sports physician and physical therapist

Physical tests	

Physical examination	Height, weight, waist and hip circumferences, four skinfolds (biceps, triceps, suprailiacal and subscapular)

Body composition and bone mineral density	Dual Energy X-ray (DXA) scan

Questionnaires	

Health-related quality of life	EORTC Quality of Life Questionnaire C30 (EORTC QLQ-C30) [43], EuroQol (EQ5D) [44], EORTC Chemotherapy-induced peripheral neuropathy module (QLQ-CIPN20) [45]

Physical activity	Physical Activity Scale for the Elderly (PASE) [46], Recordings of the Actitrainer accelerometer (Actigraph, Fort Walton Beach Florida, USA)

Mood disturbance	Hospital Anxiety and Depression Scale (HADS) [47,48]

Functioning in daily life	Impact on Participation and Autonomy (IPA) [49]

Quality of Sleep	Pittsburgh Sleep Quality Index (PSQI) [50]

Return to work	Return to work questionnaire

Moderating variables	Questionnaire about pre-illness lifestyle, current attitudes toward and beliefs about exercise in general

Satisfaction with the intervention	Satisfaction questionnaire

Cost questionnaires	Cost dairies

Compliance with the exercise program	Self-report and objective measures (e.g. attendance, exercise logs, target intensity)

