#### Costs from a societal perspective

Besides the costs of the exercise programmes, data on health care costs, patient and family costs, and costs of production losses are collected using cost diaries administered on a 3-monthly basis during the entire follow-up period. Health care costs include the costs of oncological care, general practice care and physiotherapy, additional visits to other health care providers, prescription of medication, professional home care and hospitalization. Patient and family costs include out-of-the-pocket expenses such as travel expenses, over-the-counter medication, and costs for paid and unpaid help. Costs related to production losses include work absenteeism for patients with paid jobs, and days of inactivity for patients without a paid job.

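### One baseline-adjusted regression of the week-12 and week-64 values is prescribed for every outcome, which does not fit return to work, a one-time event with its own at-risk group

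*Protocol article*

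**What the plan says.** Return to work appears among the secondary outcomes ("functioning in daily life, return to work, cost from a social perspective"), and Table 1 gives its instrument only as "Return to work questionnaire". Outcomes are assessed at baseline, "12 weeks after randomization (t = 1), and 64 weeks after randomization (t = 2").

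The Statistical analysis section sets one rule: "Multilevel longitudinal regression analysis will be conducted to assess changes in each outcome measure". The dependent variable is the follow-up measurement ("values corresponding with performance at t1 and t2"), and "Regression models will be adjusted for gender, baseline values, and compliance". The closing remark on missing values calls the model a linear mixed regression. No outcome is exempted, and no restriction to patients in paid work is stated.

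The cost section describes a second source of work data. Cost data, including production losses, are "collected using cost diaries administered on a 3-monthly basis during the entire follow-up period". The losses are "work absenteeism for patients with paid jobs, and days of inactivity for patients without a paid job", so the sample is expected to include patients without a paid job.

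**The concern.** A regression of repeated values on their baseline suits a level that moves up and down. Return to work is an event that a patient reaches or does not reach. Three things follow.

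- **Baseline.** Among patients still off work at t0, baseline status is the same for everyone and adjusts for nothing. If patients already back are kept in, they are modelled although they cannot have the event.
- **Who is at risk.** Patients without a paid job cannot return to one, and the rule as written sets no at-risk group.
- **Timing.** If the outcome is a status, a return at week 16 and one at week 60 give the same pair of readings: off work at week 12, back at week 64. The trial collects absenteeism data every three months, but the rule does not use them for this outcome.

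At stake is the precision and meaning of the return-to-work comparison between the two exercise intensities. The primary outcomes are not touched.

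**Working it through.** **Inputs from the article.** 140 patients per exercise group (Power calculations); readings at weeks 12 and 64 (Study Outcomes); 3-monthly diaries (cost section). The article gives no power figure for return to work. Its fatigue figure reproduces on a per-group reading: 2 × (1.960 + 0.842)² × 20² / 9² = 77.5, so 78 against the stated 80. That figure has no bearing on this outcome.

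**Assumptions, not in the documents.** Exponential time to return, hazard ratio 1.5 for high versus low-to-moderate intensity, no dropout, and every job holder at risk from randomisation. Job share and speed of return are varied.

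**Where the difference lies.** Let S(t) = 2^(−t/median) be the share still off work in the slower arm. The arms then differ by S − S^1.5. With a median of 26 weeks:

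- week 12: 0.726 − 0.619 = 0.107
- week 30: 0.449 − 0.301 = 0.148
- week 64: 0.182 − 0.077 = 0.104 (unrounded values)

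The gap is widest between the two readings. With a 52-week median the picture changes: 0.066 at week 12, 0.121 at week 30 and 0.148 at week 64. There is then less to gain from reading in between.

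**Power.** Three analyses were simulated, 1,500 trials per scenario, two-sided 5% critical value:

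- (a) the linear analysis of 0/1 status at weeks 12 and 64 (with complete data, the contrast of patient means), all patients, with those without a job coded 0;
- (b) the same, job holders only;
- (c) a log-rank test on times grouped to 13-week intervals, job holders only.

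| Job share | Returned by week 64, slower arm | (a) | (b) | (c) | (c) − (b), points | (b) − (a), points |
|---|---|---|---|---|---|---|
| 40% | 60% | 0.22 | 0.39 | 0.42 | 4 | 16 |
| 40% | 80% | 0.18 | 0.40 | 0.47 | 7 | 23 |
| 40% | 95% | 0.10 | 0.40 | 0.55 | 15 | 30 |
| 60% | 60% | 0.36 | 0.52 | 0.58 | 6 | 16 |
| 60% | 80% | 0.29 | 0.58 | 0.69 | 11 | 29 |
| 60% | 95% | 0.20 | 0.55 | 0.71 | 16 | 35 |
| 80% | 60% | 0.53 | 0.65 | 0.71 | 6 | 11 |
| 80% | 80% | 0.48 | 0.69 | 0.79 | 10 | 20 |
| 80% | 95% | 0.32 | 0.65 | 0.82 | 17 | 33 |

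Differences are taken before rounding.

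**Cross-check on (c), 60% with a job and 80% returned.** Events = 280 × 0.6 × (0.8 + 1 − 0.2^1.5)/2 = 144. Schoenfeld power = Φ(√(144/4) × ln 1.5 − 1.96) = Φ(0.47) = 0.68, against 0.69 simulated.

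**Central range.** Medians of 26 to 52 weeks mean that 1 − 2^(−64/26) = 82% down to 1 − 2^(−64/52) = 57% have returned by week 64. With 50-70% holding a job, (b) runs from 0.43 to 0.62 and (c) from 0.47 to 0.74. Allowing for simulation error (about 1.3 points on each power), the gain is about 4 to 12 points.

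**Against the waiting list.** That comparison ends at week 12, inside the first 13-week diary interval. There is one interval, which carries about the same information as status at t1, so almost nothing is gained.

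**The case against.** The best defence is that the sentence is shorthand. It follows a sentence about scored questionnaires, and Table 1 also lists items such as age and satisfaction under secondary outcomes, for which a baseline-adjusted longitudinal model makes no sense. Details of the secondary outcomes are referred to an overall design paper that is not shown, and the at-risk group and link function for one secondary outcome are ordinary content of an analysis plan. The word linear occurs only in the missing-data remark, so a multilevel logistic model is possible. The diaries are cost instruments, and not using them for another outcome is a choice.

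Much of this stands, and it limits what may be claimed. A reader might infer any of the following, and the documents support none of them.

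- **Patients without a job are counted as not returned.** Neither their inclusion nor their coding is stated. Column (a) shows only what would follow if they were.
- **Returns at weeks 16 and 60 are certain to count the same.** That needs a yes/no item. The questionnaire may record a date or hours.
- **The diaries give the date of return.** They record absenteeism every three months, which supports an interval; the article does not say that exact dates are kept.
- **A known amount of power is lost, or an effective programme would look like an ineffective one.** Every rate is assumed and the like-for-like gain is modest. In the central range both analyses stay below 0.80, for an outcome on which the trial was not powered.

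The defence does not remove the mismatch. The rule is stated for every outcome, return to work is a named outcome, and nothing in the article takes its effectiveness analysis elsewhere. A logistic version would still have a baseline term that is constant in those at risk, no at-risk group, and only two reading times.

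**Conclusion.** The concern holds in a limited form. As written, the general model covers return to work and suits it poorly, because it is a one-time event with a restricted at-risk group. That conclusion needs no assumed rates.

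The size does need them. With 140 per arm, 50-70% holding a job, median return 26-52 weeks, hazard ratio 1.5 and no dropout, the diary intervals add about 4 to 12 points of power for high versus low-to-moderate intensity among job holders. Over the wider grid the gain is about 4 to 17 points, smallest when fewest have returned by week 64. Any job holders already back at t0 would reduce the number at risk in both analyses. Dilution from patients without a job, about 11 to 35 points in the wider grid, arises only if they are included as not returned. The point is worth settling before analysis, but it concerns a secondary outcome.

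**What to change.** In the Statistical analysis section, limit the multilevel model to continuous repeated outcomes and add a separate rule for return to work:

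- **Population:** patients with paid work, as recorded in the return-to-work questionnaire or cost diary, who are not back at work at t0.
- **Outcome:** time from randomisation to return, in 3-monthly intervals from the diaries.
- **Model:** discrete-time hazard model (complementary log-log link) by allocated arm, with the stratification factors tumour type and hospital.
- **Comparisons:** high versus low-to-moderate intensity over 64 weeks; exercise versus waiting list to week 12 only.

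The cost is wording and some programming. There are two small downsides. Diary gaps will widen some intervals. Employment status is not among the sociodemographic items that the article lists, so it must come from the existing questionnaires; whether they record it should be confirmed first.

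### The intention-to-treat models adjust for compliance, which arises after randomisation and is zero or undefined in the waiting-list arm at 12 weeks

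*Protocol article*

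**What the plan says.** The Statistical analysis section of the protocol article sets the principle: "Data are analyzed according to the intention-to-treat principle". It then describes a multilevel longitudinal regression for each outcome, with the follow-up values as dependent variable and, as one level, "time of follow-up measurement (values corresponding with performance at t1 and t2"). On interpretation it says: "Regression coefficients will indicate differences between interventions and control group". The next sentence fixes the covariates: "Regression models will be adjusted for gender, baseline values, and compliance".

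Table 1 shows how compliance is measured: "Self-report and objective measures (e.g. attendance, exercise logs, target intensity"). On the waiting list, Recruitment and randomization says: "After 12 weeks, patients of the waiting list control group start with the exercise programme they have been allocated to". Study Outcomes places the first follow-up at "12 weeks after randomization (t = 1").

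A separate analysis already deals with attendance: "per protocol analysis will be performed, in which only patients will be included who attained 75% of all exercise sessions".

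**The concern.** Gender and the baseline value are fixed before allocation; compliance is not. Attendance, exercise logs and achieved intensity exist only because a patient was assigned a programme and took part in it. Conditioning on them changes the question from the effect of being allocated to exercise to something else.

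For exercise versus waiting list the difficulty is acute. At 12 weeks no control has had a session to attend, so compliance almost duplicates the group indicator. The article's Discussion says the waiting list allows no long-term comparison, so 12 weeks is the only point at which exercise can be compared with control, and nothing later can rescue that contrast.

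For high versus low-to-moderate intensity, compliance is defined in both arms but is still measured after randomisation. If intensity affects attendance, adjustment removes part of the effect. If attendance and outcome share causes, adjustment introduces bias.

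The primary treatment estimates are at stake, together with the claim that they are intention-to-treat.

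**Working it through.** **Inputs from the article (Power calculations).** Fatigue difference 9, SD 20, power 0.80, two-sided alpha 0.05, sample size 80 (read as per group); 140 patients in each exercise group and 120 on the waiting list.

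**Reproducing the plan's figure.** n per group = 2 × (1.960 + 0.842)² × 20² / 9² = 77.5, so 78. The stated 80 reproduces (power 0.81 at 80). The finding does not depend on it; it only supplies the scale.

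**Assumptions not in the article.** Compliance is the fraction of sessions attended: mean 0.80 in the exercise arms, truncated at 1, and 0 for controls at 12 weeks. A single-time-point linear model stands in for the multilevel model, without a baseline term. Below, a positive effect means less fatigue.

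**What the adjusted coefficient estimates.** In a linear model with group indicators and compliance c:

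adjusted difference = unadjusted difference − (within-arm slope of outcome on c) × (difference in mean c)

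With controls at 0, the last factor is the whole mean attendance of the exercise arm. The adjusted coefficient is therefore an extrapolation to zero attendance.

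**Standard error, one exercise arm versus control.**

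- Unadjusted: √[400 × (1/140 + 1/120)] = √6.19 = 2.49.
- Adjusted: √[6.19 + (mean c)² × 400 / (280 × SD(c)²)].
- Nominal attendance SD 0.20: truncation gives mean 0.783 and SD 0.173, so √[6.19 + 0.614 × 400 / (280 × 0.0300)] = √35.4 = 5.9. Simulation gave 6.0.
- Nominal SDs of 0.10, 0.15 and 0.25 gave 10.1, 7.3 and 5.2 in simulation.

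**Estimates by scenario** (attendance SD 0.20, 2,000 replicates; the shared factor has correlation 0.4 with the outcome and 0.4 with attendance before truncation):

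| Scenario | Unadjusted (rejection rate) | Adjusted (rejection rate) |
|---|---|---|
| A. Benefit wholly through sessions attended | 9.1 (0.95) | 0.2 (0.04) |
| B. Benefit unrelated to attendance, no shared cause | 9.0 (0.95) | 9.1 (0.34) |
| C. As B, with a shared cause | 9.0 (0.95) | −5.0 (0.13) |
| D. No true effect, with a shared cause | 0.0 (0.05) | −13.9 (0.67) |

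The formula agrees:

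- A: the slope is 9 / 0.78 = 11.5, and 11.5 × 0.783 = 9.0, which cancels the effect.
- C: the slope is (8 × 0.4 × 0.2 × 0.841) / 0.0300 = 17.9. Here 8 is 0.4 × 20, and 0.841 is the share of attendance values not truncated. Then 9 − 17.9 × 0.783 = −5.0.
- D: 0 − 14.0 = −14.0.

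A second set of runs, with attendance SD 0.15, gave the same pattern: about 0 with power 5% when benefit is proportional to attendance, and 9 with power 24% when it is unrelated. With a shared factor (correlation 0.5 with attendance, 0.3 with outcome) the adjusted estimate was an apparent harm of about 8 to 17 points.

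**High versus low-to-moderate.** Suppose mean attendance is 0.65 and 0.85, or 0.647 and 0.824 after truncation, a difference of −0.177. With the shared cause and no true difference, the adjusted contrast is 0 − 17.9 × (−0.177) = 3.2 points. With benefit wholly through sessions, the real difference of 11.5 × (−0.177) = −2.0 is adjusted away to 0.1. A milder case (10-point gap, correlations 0.5 and 0.3) gives a spurious 1.4 points.

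**If controls are coded missing.** A complete-case fit drops every waiting-list row, and the contrast cannot be estimated.

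**The case against.** The strongest reply accepts the defect and disputes its certainty and size.

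- **Bias is not inevitable.** In scenario B the coefficient still targets the randomised effect. This stands, although the standard error is then about 2.4 times larger (6.0 against 2.5).
- **The coding of controls is not stated.** If attendance were centred within the exercise arms and controls set to 0, a rerun gave 8.9 to 9.0 points, SE 2.5 and power about 95%, even with a shared cause or with benefit proportional to attendance. This shows how far the sizes depend on coding. The article does not specify such centring, so it cannot be relied on.
- **The planned model includes the baseline value, which absorbs some shared prognosis.** With the second set of correlations and controls at 0, the apparent harm of 8.2 points fell to 4.3 and 0.5 at correlations of 0.5 and 0.7 between baseline and the shared factor. At 0.9 the estimate was a benefit of 5.5. The spurious high-versus-low difference shrank from 1.5 to 1.2, 0.8 and 0.4. The largest figures are therefore an upper range, but every value still misses the true 9.
- **The article does not say that intensity lowers attendance.** It gives both programmes the same frequency, duration and counselling and reports that earlier programmes were well tolerated. This stands: the bias between the two exercise arms is possible rather than shown, and is smaller than for the waiting-list contrast.

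**Conclusion.** The concern holds: the covariate rule is wrong as written. It is a stated choice and not a detail left to the analysis plan. Nothing in the article confines compliance to the per-protocol or another secondary model, and it conflicts with the declared intention-to-treat principle.

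With raw attendance and controls coded 0, the exercise-versus-control estimate at 12 weeks can range from unbiased but imprecise, through zero, to the wrong sign. Which of these occurs depends on the assumed link between attendance, benefit and prognosis, and on how much prognosis the baseline value captures. Zero or undefined compliance among controls is inferred from the start of their programme after 12 weeks, since the article gives no coding. The case for removing the covariate needs none of these magnitudes.

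**What to change.** Delete compliance from the covariate sentence for the intention-to-treat models and limit adjustment to variables fixed before randomisation: the baseline value of the outcome and gender. Adding the stratification factors, tumour type and hospital, would be sensible but is not needed to cure this defect.

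Report compliance descriptively by arm and confine its analytic use to the planned per-protocol analysis or another labelled secondary analysis. If the effect of exercise actually received is of interest, a complier-average estimate using randomisation as the instrument is an option.

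The change costs one sentence of analysis wording. It needs no extra patients or data and leaves the sample size as it is.
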